The literature relating to the accuracy of digital vaginal examination versus ultrasound as the gold standard is presented in Table 1. Accuracy varied from 20% to 75% [4,12-19]. The authors of a prospective study of a hundred women which set out to evaluate the learning curves of digital examination and transabdominal ultrasound to determine the fetal head position in labour, reported that it was easier to become skilled in ultrasonography than digital examination [19]. Few studies have addressed error rates in ultrasound determined fetal head position among novice ultrasonographers and only two studies have reported error rates of transabdominal scan within a research setting (6.8% and 7.9% respectively) with another study reporting inability to diagnose the fetal head position in 15% [16,17,19]. We found only two studies evaluating the role of ultrasound assessment to determine the fetal head position before instrumental deliveries [20,21]. Akmal *et al.* compared the accuracy of vaginal examination to transabdominal ultrasound examination in 64 women undergoing instrumental delivery and found that vaginal examination was incorrect in 27% cases with errors being more likely with occipito-posterior positions and if the head was at the level of the ischial spines [20]. Wong *et al.* carried out a randomized trial of fifty women undergoing vacuum extraction for prolonged second stage where women were randomly allocated to either digital examination (n = 25) or digital examination together with transabdominal intrapartum ultrasound (n = 25) prior to vacuum extraction by the attending obstetrician [21]. A midwife measured the distance between the centre of the chignon and the flexion point immediately after delivery. The mean distance between the centre of the chignon and the flexion point was 2.1+/−1.3 cm in the group with digital examination and ultrasound assessment and 2.8+/−1.0 cm in the group with digital examination alone, a small but statistically significant difference [21].

**Table 1 T1:** Studies evaluating accuracy of transvaginal digital examination compared to ultrasound in diagnosing the position of the fetal head in labour

**Author, citation**	**Study design**	**Exposures**	**Outcome measures**	**Results**	**Conclusions**

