### Outcome measures

#### Primary outcome

The primary outcome measure is incorrect diagnosis of the fetal head position. Most errors of clinical diagnosis are where the position is classified as occipito-anterior but is in fact occipito-transverse or occipito-posterior. Incorrect diagnosis of the fetal head position will be established according to any of the following criteria:

i) Position of the head at the time of delivery

If the position of the fetal head was classified as occipito-anterior and is delivered occipito-posterior the diagnosis of the fetal position will be considered incorrect.

ii) Instrument markings on the neonatal head and face

The neonatologist or midwife who attends the delivery will examine the baby. He/she will be asked to record the markings of the instrument on a drawing of the head and lateral aspects of the face (Figure 2). The recorded markings will be used to indicate misplacement of the instrument at a distance from the flexion point (vacuum) or over the face (forceps). If for example the recorded position prior to instrumental delivery was occipito-anterior and the instrument placement suggests an occipito-transverse or occipito-posterior position the diagnosis of the fetal position will be considered incorrect. Furthermore, the diagnosis will be considered incorrect if the markings are more than 45^0^ from the documented fetal head position.

iii) Position at caesarean section

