**Figure 2 F2:**
[figure not shown]
Data sheet: instrument markings on neonatal head and face.

If the delivery is completed by caesarean section the operator will record the position of the head at delivery. If the position of the fetal head was defined as occipito-anterior but is in an occipito-posterior position at caesarean section the diagnosis of the fetal position will be considered incorrect. This information will be cross-referenced with the instrument markings recorded by the neonatologist in cases where there was an initial attempt at instrumental delivery.

The primary outcome will be validated independently by a single investigator who is not involved in scanning or the delivery by reviewing the trial documents (fetal head position recorded by the obstetrician, diagrammatic records of instruments markings on the neonate and documented position of the head position at delivery as described above). Trial allocation will be concealed from this person. Two additional data items will be recorded; i) where the position has been correctly identified the application of the instrument will be classified as optimal or sub-optimal based on the instrument markings and ii) where there is discordance between the findings of the clinician and ultrasonographer the researcher will record whether the ultrasound finding was accepted or not.

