#### Sample size

The rate of inaccurate diagnosis (difference of more than 45 degrees) was hypothesized to be 20% in the usual care arm (clinical assessment alone) and 10% in the intervention arm (clinical assessment and ultrasound). With 225 women per arm, the study will have 80% power with 5% two-sided alpha, to detect the hypothesized 10% difference. However, it is possible that inaccuracy rates are being under- or over- estimated. It could be argued that any difference in effect on the primary clinical outcome would be worth detecting. Rather, given the need for timely delivery of evidence, we have specified detectable differences for realistic sample sizes recruited within a reasonable time frame within the constraints of the available funding.

The combined annual birth rate for the two recruiting hospitals is 13,500, and around 40% of women will be nulliparous, of whom 30% will have an instrumental delivery. We estimate that there will be a total of 3240 instrumental deliveries among nulliparous women over the 24 month recruitment period based on hospital statistics for 2007. Allowing for 30-50% exclusion and non-consent, 95% collection of the primary outcome, and recruiting for 24 months during office hours yields a conservative estimate of 450 participants (225 per arm) for analysis. This would enable detection of a between-group difference of 10–13 percentage points (odds ratio 0.44 to 0.55) with 80% power and 5% two-sided alpha, and would certainly be considered by women and clinicians as worthwhile. These conservative recruitment estimates take account of eligibility criteria, non-english speaking women and the potential difficulty of randomisation and ultrasound evaluation in the context of suspected “fetal distress”.

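### Criterion ii of the primary outcome can score a discordance of 45 degrees or less, or a poorly applied instrument after a correct diagnosis, as a misdiagnosis

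*Protocol article*

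**What the plan says.** Under Primary outcome, one positive criterion is enough: "Incorrect diagnosis of the fetal head position will be established according to any of the following criteria". Criteria i and iii compare the recorded position with the head position seen at vaginal delivery or at caesarean section. Both are worded for a recorded anterior position that turns out to be posterior.

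Criterion ii works from instrument marks drawn on a diagram of the head and face. It says that the marks are "used to indicate misplacement of the instrument at a distance from the flexion point (vacuum) or over the face (forceps". Two scoring statements follow:

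- The first is given as an example. The recorded position was anterior and "the instrument placement suggests an occipito-transverse or occipito-posterior position the diagnosis of the fetal position will be considered incorrect".
- The second is introduced as an addition: "the diagnosis will be considered incorrect if the markings are more than" 45 degrees from the documented position.

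The validation paragraph after Figure 2 has one investigator review the recorded position, the marks and the documented head position at delivery. It states: "Trial allocation will be concealed from this person". It also adds a separate data item: "where the position has been correctly identified the application of the instrument will be classified as optimal or sub-optimal based on the instrument markings".

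The Sample size section plans on a single definition: "The rate of inaccurate diagnosis (difference of more than 45 degrees". The assumed rates are 20% with usual care and 10% with the scan, at 225 women per arm.

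**The concern.** The outcome is meant to measure diagnosis, but criterion ii observes where the instrument went. The two can part company in two ways.

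First, the example trigger carries no angle. The 45-degree rule is added to it and does not limit it, so the outcome as defined can be wider than the outcome the trial was sized on.

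Second, an operator may diagnose the position correctly and apply the instrument badly. The protocol recognises this, since it grades application separately. But that grade is given only after the diagnosis has been judged correct, and the judgement rests partly on the same marks. No rule separates the two explanations, and the opening reference to misplacement invites a reviewer to score a placement fault as a diagnostic one.

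At stake are the planned power and the meaning of a positive result, which could reflect better diagnosis, better placement or both.

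**Working it through.** **1. Angles.** The Usual care arm section records position on a clock of 24 sections of 15 degrees and then uses eight classes. Eight classes on a circle lie 360/8 = 45 degrees apart. If a recorded anterior position includes left anterior (LOA), and the marks suggest left transverse (LOT), the nominal discordance is 45 degrees. That is not more than 45, so the second trigger and the sample size definition do not count it, but the first trigger does. If the classes share the sections equally (24/8 = 3 each, an assumption), two marks either side of a class boundary can be only 15 degrees apart. If anterior means direct anterior only, the nominal gap to transverse is 90 degrees and the conflict largely disappears. The text does not say which is meant.

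**2. The plan's own figure.** Inputs from Sample size: p1 = 0.20, p2 = 0.10, two-sided 5% alpha, 80% power. The mean rate is 0.15.

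n = [1.96 × √(2 × 0.15 × 0.85) + 0.842 × √(0.16 + 0.09)]² / 0.10² = 199 per arm, or 219 with continuity correction. The stated 225 agrees with the corrected figure. Power at 225 is 84.6% uncorrected and 81.3% corrected.

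**3. Equal misscoring in both arms.** Let f be the share of correctly diagnosed women scored incorrect through criterion ii. The documents give no value, so f is assumed. The observed rate is p + f(1 − p), that is 0.20 + 0.80f and 0.10 + 0.90f. The difference shrinks to 0.10 × (1 − f).

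| f | Usual care | Scan | Difference (points) | Odds ratio | Power at 225 | Corrected power | n per arm for 80% (uncorrected) |
|---|---|---|---|---|---|---|---|
| 0 | 20.0% | 10.0% | 10.0 | 0.44 | 84.6% | 81.3% | 199 |
| 2% | 21.6% | 11.8% | 9.8 | 0.49 | 79.8% | 76.0% | 227 |
| 5% | 24.0% | 14.5% | 9.5 | 0.54 | 72.6% | 68.4% | 270 |
| 10% | 28.0% | 19.0% | 9.0 | 0.60 | 61.5% | 57.2% | 348 |
| 20% | 36.0% | 28.0% | 8.0 | 0.69 | 44.4% | 40.4% | 533 |

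**4. Unequal misscoring.** The Intervention arm section has the operator told the scan result, and Table 1 cites a trial concluding that ultrasound improves cup placement. So f may be lower in the scan arm. The observed difference is 0.10 + 0.80f(usual) − 0.90f(scan). It exceeds 10 points once f(scan) is below 8/9 of f(usual).

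- With 10% v 5%, the rates are 28.0% v 14.5%, a difference of 13.5 points. The odds ratio is (0.145/0.855)/(0.28/0.72) = 0.436, against 0.444 with no misscoring. The exaggeration is therefore clear in percentage points and slight on the odds ratio scale.
- With 20% v 10% and no true difference in diagnosis (20% in both arms), the rates are 36.0% v 28.0%. The chance of a significant result is about 44%.

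**The case against.** The strongest reply is that the misplacement sentence is not a scoring rule. In criterion ii a diagnosis is called incorrect only for positional discordance, and other poor placement goes to the optimal/sub-optimal item. That stands. A reader might infer that any mark away from the flexion point, or over the face, makes the diagnosis incorrect; the text does not say so. A reader might also infer that the same baby must be both an incorrect diagnosis and a correct one with sub-optimal application. Read in sequence, the grade follows only from a diagnosis already judged correct, so that contradiction is not established. What remains is that the trigger has no angle and that nothing separates poor application from misdiagnosis once a trigger fires.

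A second reply is that f has no source. This is also right. The Literature review reports distances from the flexion point ("The mean distance between the centre of the chignon and the flexion point was" 2.1 cm with ultrasound and 2.8 cm without). A mean distance does not show how often marks imply another position, and it says nothing about forceps.

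Third, the planned 20% and 10% might already include errors inferred from marks. Their exact source is not stated. The validation study, which the article says informed the power calculation, used an expert scan as its reference, so nothing shown suggests it; but it cannot be excluded, and the losses above would then not apply as computed.

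Fourth, the article is condensed and the reviewer's detailed instruction may exist elsewhere. That may be so, but the criterion as published differs from the sample size definition. Blinding the reviewer limits biased judgement; it does not supply the missing rule.

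**Conclusion.** The point holds in a limited form. Criterion ii has a trigger without an angle that can score a discordance of 45 degrees or less, at odds with the planning definition, provided that anterior includes left and right anterior. Either trigger can also score a correct diagnosis with poor application as an error.

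The size is conditional. With equal misscoring of an assumed 5% or 10%, power falls from about 85% to 73% or 62% (81% to 68% or 57% with continuity correction). It is tempting to conclude that the comparison is simply diluted. The documents do not support that, because dilution needs similar misscoring in both arms and the protocol's own evidence points to better placement with the scan. The effect on diagnosis could instead be overstated, and a pure placement benefit could pass for a diagnostic one. This is an ambiguity in the endpoint worth removing; a known loss of power has not been shown.

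**What to change.** 1. Within criterion ii, score the diagnosis incorrect only if the head position implied by the markings is more than 45 degrees from the recorded position. Keep the anterior-to-transverse or posterior case only as an illustration of that rule.
2. State that lesser discordance, and misplacement by distance or over the face alone, does not make the diagnosis incorrect and is graded only under the optimal/sub-optimal item. Put the same words in the blinded reviewer's instruction.
3. Add a sensitivity analysis of the primary outcome that does not count women classed incorrect by criterion ii alone. The rewording cannot separate poor application from misdiagnosis beyond 45 degrees, and this analysis shows how much the result depends on such cases.

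The cost is one reworded criterion, one scoring instruction and one extra analysis, with no new data. Observed error rates may be somewhat lower. The sensitivity analysis will have fewer events, because criteria i and iii are worded only for anterior-posterior errors; in the validation study these were 8 of the 25 incorrect clinical diagnoses (32%). It should be read for consistency of direction and not for significance.

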### Intervention

#### Usual care arm

Women allocated to receive usual care will be managed according to Royal College of Obstetricians and Gynaecologists (RCOG) guidelines and the local hospital protocol [3]. The women will be assessed by abdominal and digital vaginal examination prior to instrumental delivery. Following clinical assessment, location of the fetal occiput in relation to pelvic landmarks will be indicated visually by way of a cross on a data sheet depicting a circle, like a clock, divided into 24 sections, each of 15 degrees (Figure 1). The position will then be classified as OA for direct occipito-anterior, ROA and LOA for right and left occipito-anterior respectively; OP for direct occipito-posterior, ROP and LOP for right and left occipito-posterior; ROT and LOT for right and left occipito- transverse respectively. The obstetrician may then proceed to instrumental delivery. The full clinical assessment, delivery procedure, delivery outcome and measures of early morbidity will be recorded on a standard instrumental delivery proforma. The mother and the neonate will be followed-up until hospital discharge.

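### Criterion ii of the primary outcome makes no allowance for head rotation between the recorded diagnosis and instrument application, so a correct malposition diagnosis can be scored as an error

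*Protocol article*

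**What the plan says.** All references are to the protocol article.

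- **When the reference is recorded (Intervention, Usual care arm).** "Following clinical assessment, location of the fetal occiput in relation to pelvic landmarks will be indicated visually by way of a cross" on a clock-type sheet with 15-degree sections. This happens before the instrument is applied. The Intervention arm section says those women are managed in the same way, with a scan immediately before or after the clinical examination.
- **How the criteria combine (Primary outcome).** "Incorrect diagnosis of the fetal head position will be established according to any of the following criteria". One criterion is enough.
- **Criterion i.** The error is defined in one direction: "If the position of the fetal head was classified as occipito-anterior and is delivered occipito-posterior".
- **Criterion iii.** Also one direction: "If the position of the fetal head was defined as occipito-anterior but is in an occipito-posterior position at caesarean section".
- **Criterion ii.** The markings are first described as a check on placement: "The recorded markings will be used to indicate misplacement of the instrument at a distance from the flexion point (vacuum) or over the face (forceps"). The rule then adds: "Furthermore, the diagnosis will be considered incorrect if the markings are more than" 45 degrees from the position on record. No direction is specified and rotation is not mentioned.
- **What the masked validator reviews (Primary outcome, independent validation).** "fetal head position recorded by the obstetrician, diagrammatic records of instruments markings on the neonate and documented position of the head position at delivery".

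The article never mentions rotation of the fetal head. Its only use of the word is for turning the ultrasound probe.

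**The concern.** The reference is a single position fixed at one moment, while the markings reflect where the head was when the instrument went on. If the head turns in between, spontaneously or by the operator's hand, the two can differ by more than 45 degrees although the diagnosis was right when made.

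Criteria i and iii are protected against this because an OP or OT head that comes to OA is no error under either. Criterion ii has no such protection and can produce a primary-outcome event by itself.

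The women exposed are those whose malposition was correctly recognised. The trial expects the scan to enlarge that group, so the misclassification need not be balanced between arms and could dilute the effect the trial is designed to detect.

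**Working it through.** **1. Can the listed documents separate a true error from a false one?** Two situations:

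| | Head at examination | Recorded | What follows | Diagnosis in truth |
|---|---|---|---|---|
| A | OP | OP | turns to OA before application | correct |
| B | OA | OP | no rotation | incorrect |

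Both can leave the same three items for the validator: OP recorded, markings of an OA application, OA at delivery. Criterion i flags neither. Under criterion ii, a strict reading scores both as incorrect and a lenient reading passes both. Only a record of rotation separates them.

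**2. The plan's own figure.** From Sample size: 20% v 10%, 225 per arm, two-sided 5%, 80% power. Power = Φ[(d − 1.96·se0)/se1], where d = 0.10, se0 = √(2 × 0.15 × 0.85/225) = 0.03367 and se1 = √((0.20 × 0.80 + 0.10 × 0.90)/225) = 0.03333.

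- Uncorrected: (0.10 − 0.06598)/0.03333 = 1.02, so power is 84.6%; 199 per arm would give 80%.
- With continuity correction: power is 81.3%; 219 per arm would give 80%. The stated 225 is consistent with this.

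**3. Effect of mis-scoring.** Let e be the true error rate in an arm (20% or 10%), m the share of heads that are OP/OT, s the share of errors that occur in OP/OT heads, and g the share of correctly diagnosed OP/OT heads that turn and are then scored as incorrect.

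- Correctly diagnosed OP/OT heads: m − s·e
- Observed error rate: e + g(m − s·e)
- Observed difference: 10 points × (1 − g·s)

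The documents give none of m, s or g. The Primary outcome section does say that most clinical errors are OT or OP heads called OA, which points to a high s. Assumed ranges: m = 30-50%, s = 80-100%, and the same g in both arms.

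| g | Excess false errors with ultrasound (points) | Observed difference (points) | Power at 225 per arm, uncorrected |
|---|---|---|---|
| 0 | 0 | 10 | 84.6% |
| 5% | 0.4-0.5 | 9.5-9.6 | 77-80% |
| 10% | 0.8-1.0 | 9.0-9.2 | 69-74% |
| 20% | 1.6-2.0 | 8.0-8.4 | 54-63% |

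**One case in full:** m = 40%, s = 100%, g = 10%. False errors are 0.10 × (0.40 − 0.20) = 2.0% in usual care and 0.10 × (0.40 − 0.10) = 3.0% with ultrasound. Observed rates are 22% v 13%. Here se0 = √(2 × 0.175 × 0.825/225) = 0.03582 and se1 = √((0.22 × 0.78 + 0.13 × 0.87)/225) = 0.03557, so (0.09 − 0.07021)/0.03557 = 0.556 and power is 71% (67% with continuity correction). Reaching 80% would take 279 per arm (301 with correction).

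Power falls for two reasons: the difference shrinks, and both rates move up, which increases the variance.

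**The case against.** - **Markings lie on the fetal head.** Criterion ii first describes them relative to the flexion point or the face. An instrument well placed after rotation shows no misplacement in that sense, and a validator working this way could pass it. This stands: such a case *can* be scored as incorrect, and the text does not establish that it *will* be. It does not remove the gap. The same criterion also infers an OT or OP position from placement, and sets a 45-degree limit against a position charted relative to the pelvis, without saying how one is converted to the other.
- **The information may exist elsewhere.** The Usual care arm section has the delivery procedure recorded on a proforma, which may capture rotation. The forms and figures are not shown, and an article condenses the full protocol. So it cannot be said that the validator has no means of recognising rotation. What stands is that the article lists the validator's documents and no rotation record is among them.
- **The imbalance between arms is conditional.** A reader might infer that the rule necessarily penalises ultrasound. The documents do not support that. They give no rotation rate in either arm, and the Discussion names senior support, theatre and caesarean as consequences of a recognised malposition, not rotation. It is also unclear whether the obstetrician's recorded position incorporates a scan that may come after the clinical examination.
- **Larger power losses are not supported.** One might assume that 60% of malpositions are recognised in usual care and 95% with the scan, add false errors to 20% v 10%, and arrive at power as low as 46%. With 40% of heads OP/OT, those recognition rates already imply missed malpositions of 16% v 2%, a 14-point difference, which conflicts with the planned 10. With usual care held at 20% and equal OA-head errors in both arms, mis-scoring 20% of recognised cases gives 24.8% v 13.6% and 86% power.
- **The direction is conservative.** Under the conditions stated, the bias is toward no difference and would not create a false benefit for ultrasound.

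**Conclusion.** The gap in the definition is real. Criterion ii alone can turn a correct OP or OT diagnosis into a primary-outcome event if the head turns after the record is made, and the items listed for the validator do not distinguish this from a true misdiagnosis.

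That it falls more heavily on the ultrasound arm follows only under three conditions: the scan increases correct malposition diagnoses as hypothesised, rotation is about equally frequent in both arms, and the compared position incorporates the scan.

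The size is unknown. In the illustration, mis-scoring about 5% of correctly diagnosed malpositions is enough to bring uncorrected power to just under 80%. Those figures rest on assumed rates, and without such mis-scoring the planned power stands. The point merits a change because it touches the primary outcome, is cheap to settle in advance, and is hard to repair reliably afterwards if rotation was not recorded.

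**What to change.** Change the outcome scoring only; no change to clinical management is implied.

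1. State which recorded position is the reference in each arm, including whether it is the position before or after the obstetrician hears the scan result.
2. On the existing form, record whether the head rotated or was rotated after that entry, and the position at instrument application.
3. Apply criterion ii to the position at application. Where rotation is recorded, do not score the original diagnosis as incorrect from the markings alone.
4. Add this entry to the documents given to the masked validator.

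It would also help to state how markings on the head are converted to an angle from the reference position.

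The cost is two form fields and a short addition to the outcome definition. The downside is reliance on the operator's own entry about rotation. If the proforma already holds these items, only the scoring text and the validator's document list need to change.
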